## Abstract

**Background:**

Advanced care planning (ACP) is a process that involves thinking about what medical care one would like should individuals be seriously ill and cannot communicate decisions about treatment for themselves. The literature indicates that ACP leads to increased satisfaction from both patients and healthcare professionals. Despite the well-known benefits of ACP, it is still underutilised in Australia.

**Methods:**

The aim of this study is to investigate the effects of normalising ACP in acute and community settings with the use of specially trained normalisation agents. This is a quasi-experimental study, involving 16 sites (8 intervention and 8 control) in two health districts in Australia. A minimum of total 288 participants will be recruited (144 intervention, 144 control). We will train four registered nurses as normalisation agents in the intervention sites, who will promote and facilitate ACP discussions with adult patients with chronic conditions in hospital and community settings. An audit of the prevalence of ACP and Advanced Care Directives (ACDs) will be conducted before and after the 6-month intervention period at the 16 sites to assess the effects of the ACP service delivered by these agents. We will also collect interview and survey data from patients and families who participate, and healthcare professionals who are involved in this service to capture their experiences with ACP.

**Discussion:**

This study will potentially contribute to better patient outcomes with their health care services. Completion of ACDs will allow patients to express their wishes for care and receive the care that they wish for, as well as ease their family from the burden of making difficult decisions. The study will contribute to development of a new best practice model to normalise ACP that is sustainable and transferable in the processes of: 1) initiation of conversation; 2) discussion of important issues; 3) documentation of the wishes; 4) storage of the documented wishes; and 5) access and execution of the documented wishes. The study will generate new evidence on the challenges, strategies and benefits of normalising ACP into practice in acute and community settings.

**Trial registration:**

This project has been approved by the Hunter New England Human Research Ethics Committee (Approval No. 17/12/13/4.16). It has also been retrospectively registered on 3 October 2018 with the Australian New Zealand Clinical Trials Registry (Trial ID: ACTRN12618001627246). This study will operate in accordance with the National Health and Medical Research Council’s National Statement on Ethical Conduct in Human Research (2007) and the CPMP/ICH Note for Guidance on Good Clinical Practice.

## Introduction

Chronic disease (e.g. cardiovascular, respiratory, diabetes, dementia) contributes to more than 70% of the disease burden in Australia and the burden of chronic disease is increased with the ageing population [1, 2]. Among the patients with chronic conditions, a total of 17,372 people died after 38,905 hospitalisations representing 24% of total 165,000 hospitalisations in New South Wales (NSW) in 2011/12 [3]. The majority (76%) were emergency admissions. Although about 42% of this sub-cohort died in hospital, only 4% of them received palliative care services [3]. Given the significant impacts of rapid increase of ageing population with chronic diseases on the health of the people themselves and the resources of the health care system, understanding the issues related to end of life (EOL) care and treatment options preferred by people with chronic diseases has become a priority for health care professionals [2, 4].

Advance care planning (ACP) is a process that involves thinking about what medical care one would like should individuals be seriously ill or injured and cannot make or communicate decisions about care or treatment for themselves [5]. An Advance Care Directive (ACD) can only be made by an adult with decision-making capacity. It is a written statement by those who can make medical decisions for themselves for the time when one is unable to make decisions. It should include what is important to the person such as values, life goals and preferred outcomes [5]. It is widely considered optimal if ACP happens earlier in life, when the person is still well and capable of making decisions [6]. The benefits of ACP are well documented in Australian context and worldwide. ACP improves the quality of EOL care, patient and family satisfaction, and reduces stress, anxiety and depression in surviving relatives [7–15].

Significant work has been done to promote ACP internationally. In NSW, Australia, many resources are available about ACP and ACDs including legally binding ACD forms [5], and policies (e.g. End-of-life care and Decision-making Guidelines, A National framework for Advance Care Directives, Using Advance Care Directives, Advance Planning for quality care at end of life: Action Plan 2013–2018). Despite the well-known benefits of ACP for people, and substantial work conducted to increase the uptake of ACP, both published research [16] and our study’s initial evidence identified the following persisted problems in acute and community healthcare settings.Despite many resources available on ACP and ACDs, awareness of ACP is low and completion of ACD is very low in The Hunter New England (HNELHD) and Central Coast Local Health Districts (CCLHD). This low rate is regardless of cultural and ethnic backgrounds, and stemmed from a lack of understanding of the concept, the various terms and forms, being time consuming in the processes involved and the feeling ‘I don’t know how to do it’ [17].Adult children are the most preferred substitute-decision-maker (SDM) to husband/wife, but the existing legal and ethical frameworks do not capture the current preference of people as SDMs [18].The attitudes towards the end-of-life issues differ within the context and depending on individuals’ cultural and religious beliefs and values, and preferences for care [19].Despite education and resources available for health care professionals (e.g. doctors and nurses), they feel unconfident and unprepared, and their commitment remains minimal [16, 20]The challenges in ACP lie in the processes of: 1) initiation of conversation; 2) discussion of important issues; 3) documentation of the wishes; 4) storage of the documented wishes; and 5) access and execution of the documented wishes, and that an effective and consistent solution for increasing practice of ACP remains elusive.

The proposed intervention in this project is informed by existing evidence that complex ACP interventions have resulted in increased frequency of out-of-hospital and out-of-ICU care, increased adherence to patients’ preferences, and increased satisfaction with their health care experience [7]. We established and tested evidence from the literature and clinical experiences over the last 10 years, and concluded that normalisation of ACP by a designated person and using the patient’s own language is the optimal implementation strategy. However, this approach has only been implemented and tested by a few individual clinicians on an ad hoc basis. The proposed intervention is built on these previous findings and will provide us with an opportunity to test and evaluate this approach in a wider scale.

In this study we examine the effect of trained general (not specialised) registered nurses (RNs) to promote and normalise ACP for people with chronic conditions in hospital and community health settings. The targeted population in this project (people with chronic diseases) is aligned with targeted populations for special Advance Care Planning needs [6], which includes; Diabetes, Congestive Heart Failure, Coronary Artery Disease, Chronic Obstructive Pulmonary Disease, Hypertension, Chronic Kidney Disease, Cancer, frailty and Dementia.

## Methods/design

### Aims

The primary aim: To test the feasibility and effectiveness of normalisation of ACP for people with chronic diseases in acute and community settings.

The secondary aims are:To identify the characteristics of the most effective setting and demographics for ACP implementation.To investigate the nature and extent to which planning for future health care wishes are initiated, discussed and documented among people with chronic diseases, their family members, and RN ACP facilitators.To identify the effect of ACP on patient/SDM satisfaction with their healthcare experience.To identify factors that influence the implementation of ACP in hospital and community health settings.To assess and estimate the financial impact of normalisation of ACP on our health care system.

### Theoretical framework for the study

This project proposes an innovative approach to address the above problems by promoting ‘ACP conversations’ as part of routine (normal) clinical practice, underpinned by Normalisation Process Theory (NPT). This theory is centred on the work of embedding and of sustaining practices within interaction chains [21]. NPT focuses on what people do in the process of implementation. The theory constructs four mechanisms that explain the social process in the implementation of material practices by specialised ‘agents’. These mechanisms are coherence, cognitive participation, collective action, and reflexive monitoring (Table 1) [21].

**Table 1 Tab1:** Agents and for mechanisms for Normalisation Process Theory

Agents	Agents are individuals and/or groups who contribute to the processes that lead to implementation, embedding, and integration of new practice. For this study, agents are healthcare professionals (admitting Medical Officer, Registered Nurse, Social Workers and RN ACP facilitators). They use the NSW Health ‘ACP – Making your wishes known’ information to patients, to initiate, engage in discussion, and answer any questions.
Coherence	This involves what and how things should be done which starts with how it has been done and what we should do differently. The meaning of new practice needs to be learned, experienced and internalised by the agents. The agents in this study are provided with the opportunities to learn, experience and internalise.
Cognitive participation	When the process of coherence is internalised, the agents engage in a new practice across the context. The agents in this study are given 6 months to internalise and normalise ACP as a routine practice.
Collective action	The new practice is operated and enacted in practice. In this study, material and human resources, working relationships between agents, a degree of autonomy are closely monitored and enacted upon.
Reflexive monitoring	This is an evaluation of implementation process. The agents will engage in an evaluation of the implementation process that reflects cognitive participation and collective action. It involves both individual and group appraisal and reconfiguration of ACP practice to embed and sustain a new ACP practice.

### Design

The project is a quasi-experimental design with two groups: 1) intervention groups with RN ACP facilitators, and 2) control groups without RN ACP facilitators. See Fig. 1. Research Flow Chart below.

**Fig. 1 Fig1:**
[figure not shown]
Research flow chart

ACP will be normalised into practice for 6 months by RN ACP facilitators (normalisation agents) in nominated wards/units in acute and community settings in two Local Health Districts (LHDs). Pre and post measures (the number of people who have ACDs in medical records, Resuscitation plan, any records or notes about ACP discussion and documentation, and the concordance between the expressed wishes and the care delivered) will be obtained for the two groups. Post qualitative data (textual data, individual/focus group interviews with patients, SDMs and staff participants) will be collected and inform the challenges, strategies and implications for future policy and practice.

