### Sample size calculation

Power calculations were conducted to determine the sample size required to detect a change of at least 10% in the primary outcome; that being the proportion of completed NSW ACDs. Change was defined as the difference between the proportion at baseline, assumed to be 5% and at follow-up. Setting alpha at 5%, power at 80% and assuming a non-response rate of 25%, a sample size of 288 is needed (144 in intervention sites and 144 in control sites). Given an average admittance rate of at least 10 per week per site and over a six-month period, there is almost complete surety that the study will not be under-powered.

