### Data collection

#### Audit of ACP related practice

Data on the prevalence of ACP and ACDs will be collected through an audit of the medical records of patients admitted to the 16 research sites within the following time frames:The two month period before the introduction of the intervention period,The six month period of the intervention

The audit will initially check for the presence or absence of evidence of ACP only. Then the individuals whose medical records contain evidence of ACP will be invited to consent to access the content of ACDs (or documentation detailing personal values or specific wishes relating to medical care &/or organ donation). The audit involves the following steps.Medical records from all individuals admitted to a research site at the given times will be requested from relevant medical records departments. Records will be audited for the presence or absence of ACP only.Medical Record Numbers (MRN) of those containing evidence of ACP will be recorded. They will then be posted a letter of invitation and consent form with a pre-paid, self-addressed envelope.The individuals will return the consent form directly to the Research team. Where a completed consent form is returned, the individuals’ medical records will be re-accessed to collect information to assess the quality and completeness of any ACP or ACD, and whether there is concordance of care with the individuals expressed wishes, values and beliefs.

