### Data analysis

#### Qualitative data collection & analysis: audio-recorded individual/focus interviews

Qualitative data will be collected through audits, surveys, individual interviews and/or focus groups for both baseline and post-intervention. Content of Individual/Focus Interviews will be audio recorded (if consent given) and will be transcribed to text. Textual data will be broken down, line-by-line, and open coded i.e. specific categories relevant to the research aim and questions will be pre-identified and labelled but new categories and sub-categories will be added during analysis. Open codes will be systematically inspected and scrutinised in relation to a ‘paradigm model’ in NTP. With the research aims and questions in mind, the analysis will focus on the agents (who), coherence in conditions or context (where, when, why), coherent/collective actions/interactions (process) and reflexive monitoring (e.g. outcomes). NVivo Software will be used to handle the large amount of data.

Textual analysis (directed content analysis) will be undertaken on the following:Transcripts of interviews with people with chronic diseases & SDMsTranscripts of Individual/Focus Interviews with healthcare professionals (MO, RN, SW, RN ACP Facilitator)Completed open-ended questions from Surveys of people with chronic diseases & SDMs, healthcare professionals (MO, RN, SW, RN ACP Facilitator).

Directed content analysis will also be undertaken on information collected/recorded during delivery of the research intervention (facilitated conversations documented in medical notes and on a ‘conversation log’ and potential completion of a ‘conversation card’ and other ACP related documents, as follows:Questions, concerns, comments, reasons for uptake and refusal of the service (i.e. reasons for consenting to, or declining participation in the study).What participants already know [about ACP], and want to know.The extent and the recorded reasons for discordance [between patients’ and SDMs’ expressed wishes and the actual care they received].The experiences of patients and SDMs with ACP.The experiences of ‘normalisation agents’ [MOs, RNS &/or SWs and RN ACP Facilitators].

The reporting of qualitative measures will follow the Standards for Reporting Qualitative Research (SRQR) [25].

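### Concordance of care with wishes is listed as a pre/post two-group measure, but can be scored only in consenting patients with documented wishes, a group the intervention is meant to enlarge

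*Protocol article*

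**What the plan says.** The Design section (text after Fig. 1) names four pre and post measures. The last is concordance: "the concordance between the expressed wishes and the care delivered) will be obtained for the two groups".

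The section on the audit of ACP related practice determines who can have a value:

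- First step, all admitted patients: "The audit will initially check for the presence or absence of evidence of ACP only".
- Second step: "individuals whose medical records contain evidence of ACP will be invited to consent to access the content of ACDs". Other documentation of values or specific wishes also counts.
- Third step: "Where a completed consent form is returned, the individuals’ medical records will be re-accessed". Only here does the audit assess "whether there is concordance of care with the individuals expressed wishes, values and beliefs".

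The sample size section makes the proportion of completed NSW ACDs the primary outcome and seeks a change of at least 10%. On that change it says: "Change was defined as the difference between the proportion at baseline, assumed to be 5% and at follow-up".

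The quantitative data analysis section plans mixed-effects models to estimate the effect of the intervention. Binary outcome measures go to logistic regression, with adjustment for baseline imbalances and for clustering by site. It does not name concordance and gives it no separate treatment.

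**The concern.** Concordance has no value for a patient without documented wishes, and the audit gathers wishes for nobody else. Having a document at the post-intervention audit is itself a result of the intervention: raising ACD completion is the trial's main target, and the facilitators also enter conversation summaries in the medical record. The post-intervention subset at intervention sites would therefore contain people who would have documented their wishes anyway plus people prompted to do so. The baseline and control subsets would contain essentially the first kind only.

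If the two kinds differ in how often care matches wishes, the concordance rate moves although no patient's care has changed. Return of the consent form is a second filter, and it too may differ between groups.

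This matters because the article's case for ACP rests partly on patients receiving the care they want. A rise or fall in concordance would be read as evidence on that claim.

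**Working it through.** **Inputs from the protocol article**

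- ACD proportion at baseline: 5% (sample size calculation).
- Target change: at least 10%, read as absolute, so 15% after the intervention.
- Admissions: at least 10 per week per site, 8 sites per group, six months (26 weeks). The pre-intervention audit covers two months.
- Not stated: the share of records with any ACP evidence, the consent return rate, and any concordance rate.

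**Check of the absolute reading.** The unpooled two-proportion formula at a one-sided 5% level and 80% power gives n = (0.05 × 0.95 + 0.15 × 0.85) × (1.645 + 0.842)² / 0.10² = 108.2. Allowing for 25% non-response, 108.2 / 0.75 = 144.3, against the stated 144 per group. (A two-sided test without inflation gives 141 by the pooled formula; sidedness is not stated.) Either way the figure fits 5% against 15%. Nothing below depends on the sample size itself.

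**Numbers with an ACD, per group, before consent**

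- Pre-intervention: 10 × 8 × (2 × 52/12) = 693 records; 5% = 35.
- Post, control: 10 × 8 × 26 = 2,080; 5% = 104.
- Post, intervention: 2,080 × 15% = 312.

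With an assumed consent return of 25% to 75%, these become 9 to 26, 26 to 78 and 78 to 234. They count ACD holders only; holders of other documented wishes would add to them.

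**Shift in composition with no change in care.** Let the share with documents be p0 without and p1 with the intervention. Let concordance be a in unprompted holders and b in newly prompted holders, and suppose all unprompted holders would hold a document either way. The intervention group then reads [p0·a + (p1 − p0)·b] / p1, so the spurious shift is (1 − p0/p1)(b − a).

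With p0 = 5% and p1 = 15%, two thirds of the scored intervention patients are newly prompted and the shift is (2/3)(b − a). The rates a and b are assumptions:

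| a (unprompted) | b (newly prompted) | Intervention group reads | Spurious shift |
|---|---|---|---|
| 80% | 80% | 80.0% | 0 |
| 80% | 60% | 66.7% | −13.3 points |
| 80% | 90% | 86.7% | +6.7 points |
| 60% | 90% | 80.0% | +20.0 points |
| 90% | 60% | 70.0% | −20.0 points |

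The shares matter too. If any documented wishes were present in 20% and rose to 30% (also an assumption), the factor would be 1/3, and the 80%/60% case would shift by −6.7 points.

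**Would it look significant?** For 80% against 66.7% with 104 and 312 scored, SE = √(0.8 × 0.2/104 + 0.667 × 0.333/312) = 0.047 and z = 0.133/0.047 = 2.8. This assumes full consent return and no clustering. At 50% return z is about 2.0, and at 25% about 1.4.

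**Does the planned analysis remove it?** Subtracting the control group's pre/post change does not, because the control subset is expected to stay near its baseline composition. Covariate adjustment may reduce measured case-mix differences, but not selection on having a document or on returning the form.

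**The case against.** The strongest reply is that no test of concordance is stated. The Design section says only that the measure will be obtained, the aims do not list concordance, the quantitative section never names it, and the denominator of a non-primary measure is commonly left to an analysis plan. This stands in part: the misleading comparison is what follows if the article is applied as written, not a test it spells out. But a pre and post measure in two groups, under a general plan to model outcome measures for intervention effect, points to that comparison. The audit procedure also fixes who is measured, so no later plan can supply concordance for people whose wishes were not recorded or who did not consent.

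Three stronger readings are tempting and not supported:

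- A reader might infer that only 5% to 15% of patients can be scored. Those are ACD rates. The audit accepts other documented wishes, which raises the share, and requires consent, which lowers it. The scorable share is not stated.
- A reader might infer that the trial will show a false fall of about 13 points. That rests on assumed concordance rates, and no figure in the article gives the direction or size.
- A reader might see a conflicting second definition in the qualitative section, which covers "The extent and the recorded reasons for discordance". That is content analysis of material recorded while the intervention is delivered, a separate strand and not the audit measure.

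A further fair objection concerns the remedy. Scoring documented wishes plus concordant care over all patients does not isolate concordance either. In the 80%/60% illustration it moves from 5% × 0.8 = 4.0% to 4.0% + 10% × 0.6 = 10.0% (z about 7.6 at 2,080 per group, unclustered) with nobody's care changed. It would largely repeat the primary outcome, so it should not become the compared effect measure.

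**Conclusion.** The point holds as a structural one. Concordance as set up is conditional on two post-intervention events, having documented wishes and returning the consent form. The trial is designed to change the first and may change the second. A pre/post or between-group difference among those scored therefore cannot be read as an effect on care, and the planned adjustment does not repair it.

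The size is unknown. Using the planned ACD rates, the spurious shift is two thirds of the difference in concordance between newly prompted and unprompted document holders. It is zero if they do not differ and runs from −20 to +20 points across the assumed rates shown. The primary outcome is not affected. The change is worth making before analysis because it is cheap and prevents a misleading conclusion on a measure close to the trial's rationale.

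**What to change.** In the Design section and the audit section, state that:

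1. concordance among consenting document holders will be reported descriptively by group and period;
2. the report will show the numbers audited, with ACP evidence, and consenting;
3. the figure is conditional on having a document and on consent;
4. it will not be tested or modelled under the quantitative data analysis section as an intervention effect.

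Optionally, also report the proportion with documented wishes and concordant care. The denominator should be all audited admissions, not only those eligible under Table 3, which excludes patients who already have an ACD. Give bounds for document holders who do not consent, scoring them all as concordant and then all as not. Label the result as largely reflecting ACD uptake and not as an effect on concordance.

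The cost is a few sentences of protocol wording and a short flow of counts; the optional measure adds one derived variable with bounds. The real price is that the trial can no longer claim an effect on concordance.
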